### 9.2 Statistical Methods

#### 9.2.1 Efficacy analysis

Proportions of patients with a sustained reduction of LLM from baseline by  $\geq 50\%$  between each active treatment group and the placebo group will be compared by the Chi square test.

*Loa* parasitaemia will be compared at each point between groups using non-parametric test due to the non normal distribution of the *Loa* microfilaraemia. The General Linear Model (GLM) will also be used for the comparison of the evolution of *Loa* parasitemia in different groups.

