| Safety Evaluation                | 
On the day of treatment as well as 3 and 7 days after each treatment subjects will be evaluated clinically and for self-reported adverse events. On the day of the next treatment, subjects will be asked for adverse events experienced since day 7 after the previous treatment. Laboratory tests will be performed at screening and if indicated based on the results of the clinical investigation or based on subject reported AEs.
                                                                                                                                                                                                                                                                                                                                                                                                                                                                                                                                                                                                                                                                                                                                                  |
| Statistical Analysis             | 
The proportion of subjects with a sustainable (<math>\geq 4</math> months) reduction of LLM by <math>\geq 50\%</math> of the baseline value by treatment group across all subjects and by initial microfilaria load, will be compared with the Chi-squared test. Comparison of L. loa mf/ml between treatment groups at each time point with non-parametric tests due to non-normal distribution of mf loads. General linear model for analysis of the evolution of microfilaria load in time in each treatment group.
                                                                                                                                                                                                                                                                                                                                                                                                                                                                                                                                                                                                                                                             |

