#### 6.2.4.2 Randomization

Whether or not a subject's microfilaria count drops by  $\geq 50\%$  of pretreatment values may depend on the initial microfilaria burden.

Of particular interest for this study are those, albeit rare, subjects with pretreatment LLM of  $>30000$ . Thus, if more than 60 subjects have qualified for participation in the study, the 60 subjects with the highest microfilaria counts will be selected for the study and randomized taking into account the requirement for similar distribution of pre-treatment LLM in the three treatment arms. At least 5 of the 20 subjects enrolled in each treatment arm should have a screening LLM of  $>30000$  mf/ml.

To take into account that the drop in LLM may be dependent on the pre-treatment LLM, randomization will be by strata defined by the pre-treatment microfilaremia level obtained at screening, see section 6.1.3.2. The microfilaremia strata will be:

- 15 001 to 30 000 mf/ml
- 30 001 to 50 000 mf/ml
- $\geq 50 001$  mf/ml.

A person not involved in the treatment or follow up of the subjects will generate three randomization lists i.e. pairs of randomization number and treatment assignment, one for each of the three strata.

Given the low prevalence of subjects with LLM  $\geq 30001$  and even more so  $\geq 50001$ , the number of subjects in these microfilaremia strata is likely to be small. To ensure equal distribution of the subjects in each microfilaremia stratum across the three treatment arms, randomization will be performed in blocks of three, i.e. among three success randomization numbers, one will be assigned to placebo treatment, one to 2 doses of albendazole and one to 6 doses of albendazole.

Subjects who have qualified and have been selected for the study will be assigned the next unassigned number on the randomization list for their stratum in the order of their subject number.

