## 9 DATA ANALYSIS

### 9.1 Sample Size Justification

A positive response in a subject is defined as a drop in LLM from baseline values by  $\geq 50\%$  lasting at least 4 months. Assuming that in the population less than  $1/10^6$  subjects will have a positive response if randomized to the placebo group and at least 50% of the subjects will have a positive response if randomized to the 6 dose albendazole treatment regimen, a sample size of 16 subjects in each treatment arm will provide at least 90% power to detect statistically significant (two-sided  $\alpha=0.025$ ) differences between the placebo group and the 6 dose albendazole treatment group. The same assumptions were made for the 2 dose albendazole treatment regimen so that the same power and sample size considerations apply to the comparison between placebo and the 2 dose albendazole treatment. An alpha value of 0.025 was chosen since two comparisons (placebo vs. 2 doses of albendazole, placebo vs. 6 doses of albendazole) will be performed. Based on prior experience, a drop out rate of approximately 20% is expected, resulting in a sample size of 20 subjects for each of the three treatment arms.

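### Randomisation is stratified by microfilaraemia but the primary chi-square test is not; a stratified test would be a modest, cheap efficiency gain

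*Protocol*

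**What the plan says.** Section 6.2.4.2 of the protocol (Randomization) gives its reason for stratifying: "To take into account that the drop in LLM may be dependent on the pre-treatment LLM". Accordingly, "randomization will be by strata defined by the pre-treatment microfilaremia level obtained at screening". There are three strata: 15 001 to 30 000, 30 001 to 50 000, and 50 001 mf/ml or more. Within each, "randomization will be performed in blocks of three", one number per arm. The same section adds: "At least 5 of the 20 subjects enrolled in each treatment arm should have a screening LLM of" more than 30 000 mf/ml. That is a floor for the two upper strata taken together.

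Section 9.2.1 (Efficacy analysis) defines the primary comparison. Proportions with a sustained reduction of at least 50% "between each active treatment group and the placebo group will be compared by the Chi square test". It names no stratum, covariate or stratified method. The Statistical Analysis row of the tabular overview (section 1) is wider. There the proportion "by treatment group across all subjects and by initial microfilaria load, will be compared with the Chi-squared test". Section 7.1.2 splits secondary variables by stratum.

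On the error rate, section 9.1 says: "An alpha value of 0.025 was chosen since two comparisons". The sample size there assumes a placebo response below 1/10^6 and an albendazole response of at least 50%, with 16 evaluable of 20 enrolled per arm.

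**The concern.** Balancing the arms on a prognostic factor removes that factor's variation from the difference between arms. A pooled chi-square still counts the variation in its variance. When strata differ in response, the test is therefore conservative: its true size falls below the nominal 0.025 and some power goes unused.

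The separate chi-square comparisons by load in the overview do not recover this. They are subgroup tests, they are absent from section 9.2.1, and nothing combines them into one stratum-adjusted answer. With 20 subjects per arm and about 20% expected to drop out, a few points of power are worth having if they cost nothing else.

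**Working it through.** **Inputs from the protocol.** Two-sided alpha 0.025 per comparison (chi-square critical value 5.024); 16 evaluable and 20 enrolled per arm; planning rates about 0% v 50%; three strata with equal allocation. The protocol gives neither stratum sizes nor stratum-specific rates. Those below are assumptions.

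**The protocol's own figure first.** The pooled-variance formula gives n = [2.241·√(2·0.25·0.75) + 1.282·√(0.5·0.5)]² / 0.5² = 16.2, so 17 per arm; the protocol has 16. Dropout: 16/(1 − 0.20) = 20. With no placebo responders and x albendazole responders, Pearson's statistic is 2nx/(2n − x). At n = 16, x = 4 gives 4.57 and x = 5 gives 5.93, so five responders are needed. P(X ≥ 5 | 16, 0.5) = 0.962. The stated 16 for at least 90% power is sound for an uncorrected chi-square.

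**The two tests.** For equal arms of n, with n_k per arm and m_k responders in stratum k over both arms, and M = Σm_k, both tests use D = (albendazole responders) − M/2.

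- Pearson: D² / [M(2n − M)/(8n)]
- CMH, no continuity correction: D² / Σ [m_k(2n_k − m_k)/(4(2n_k − 1))]

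The numerators are equal. Only the CMH denominator leaves out between-stratum variation.

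**Simulated power** (at least 200,000 trials per row; rates listed from lowest to highest stratum):

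| Per-arm strata | Placebo v albendazole, % | Chi-square | CMH |
|---|---|---|---|
| 8/4/4 (16) | about 0 v 50 throughout (planning rates) | 0.962 | 0.963 |
| 12/5/3 (20) | about 0 v 50 throughout | 0.994 | 0.994 |
| 12/5/3 | 20/5/0 v 75/30/10 | 0.749 | 0.791 |
| 12/5/3 | 5/10/30 v 35/65/90 | 0.772 | 0.816 |
| 10/5/5 (20) | 30/10/5 v 75/50/40 | 0.694 | 0.738 |
| 10/5/5 | 20/5/0 v 75/30/10 | 0.655 | 0.747 |
| 12/5/3 | 12/8/5 v 55/45/35 (moderate gradient) | 0.736 | 0.736 |
| 12/5/3 | 10 v 50 throughout | 0.742 | 0.739 |
| 10/4/2 (16) | 10 v 50 throughout | 0.635 | 0.609 |

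With strong gradients the gain at 20 per arm is 0.791 − 0.749 = 4 points in a typical case and 0.747 − 0.655 = 9 points in the largest. With the moderate gradient it is 0 to 1 point. At 16 per arm split 10/4/2, CMH loses about 1.5 points with the moderate gradient and 0.635 − 0.609 = 2.6 points with none.

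**Simulated size** (nominal 0.025; the same rates in both arms):

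| Per-arm strata | Common rates, % | Chi-square | CMH |
|---|---|---|---|
| 10/5/5 | 20 throughout | 0.023 | 0.024 |
| 10/5/5 | 40/10/5 | 0.014 | 0.024 |
| 10/5/5 | 60/10/5 | 0.008 | 0.023 |
| 12/5/3 | 20/5/0 | 0.014 | 0.015 |
| 12/5/3 | 5/10/30 | 0.009 | 0.012 |

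The result depends on the null rates chosen. At low response rates (last two rows) both tests fall well under 0.025, because small counts make either one conservative.

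**The by-load comparison in the overview.** Take 5 v 5 subjects above 30 000 mf/ml (the stated minimum) and 0% v 50%. Then 2nx/(2n − x) is 4.29 at x = 3 and 6.67 at x = 4. At least 4 of 5 must respond, so power is (5 + 1)/32 = 19%.

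**The case against.** The case for leaving the plan alone is substantial.

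- **The chi-square is valid.** With blocks of three within strata it errs only on the conservative side. A reader might infer that ignoring the strata inflates false positives; neither the design nor the simulations support that.
- **Under the protocol's planning rates nothing is lost.** With almost no placebo response the tests agree to about 0.1 point. A gain needs both placebo responders and a strong gradient, and section 6.2.4.2 says only that the fall may depend on starting LLM. Reading that as an expected strong dependence goes beyond the text.
- **Baseline load is not ignored.** The overview compares the primary proportion by load and section 7.1.2 splits secondary variables by stratum.
- **The upper strata need not be tiny.** Five per arm is a minimum for both together, and section 6.1.3.4 selects the 60 highest counts if more than 60 qualify. Treating five or fewer as a fact is unsupported.

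All of this stands, and it limits the point to efficiency. It does not remove the point, because placebo response may well exceed one in a million. Section 6.2.2 cites untreated geometric means ranging from 32% to 192% of pretreatment over 6 months, as the reason for having a placebo arm. The endpoint in section 5.2 also counts a sustained drop starting at any time after the first dose. Nor is this merely detail left to an analysis plan, since section 9.2.1 itself names the primary test.

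**Conclusion.** The mismatch between a stratified design and an unstratified primary test is real, and its consequence is modest. Under assumed stratum sizes and rates, CMH gains about 0 to 9 points of power at 20 per arm, with about 4 typical of strong gradients. It gains nothing at the planning rates. It can cost up to about 3 points at 16 evaluable per arm when stratum effects are weak or absent. The size of the gain cannot be fixed more closely, because the protocol supplies no stratum sizes or stratum-specific response rates. The planned test does not threaten type I error control, and the stated sample size is not called into question here.

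**What to change.** In section 9.2.1, and identically in the overview, make the primary test of each albendazole arm against placebo a CMH test stratified by the randomisation strata, two-sided 0.025, without continuity correction. Report the stratum-weighted risk difference with its confidence interval for each comparison, and keep the plain chi-square as a sensitivity analysis.

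Decide before unblinding, and without reference to outcomes, whether the two strata above 30 000 mf/ml are pooled. Either pool them outright or state a minimum stratum size that triggers pooling. An unquantified sparseness rule would leave a data-dependent choice inside the primary test.

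The cost is a few sentences in two places, with no new data, visits or subjects. On timing, the appended amendment records that the blind was lifted after month 18. If the change was not fixed before then, the chi-square should stay as the pre-specified test and CMH be reported as a labelled supportive analysis.

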| Study Treatment                  | 
Albendazole tablets (200 mg) and matching placebo
 
Administration: 800 mg albendazole orally every two months 0 (group 1, placebo), 2 (group 2, treatment regimen 1) or 6 times (group 3, treatment regimen 2).
 
Albendazol has a well-established excellent safety profile which allows it to be administered without medical supervision not only to infected, but also to uninfected subjects during the mass treatment of populations living in areas endemic for LF.
                                                                                                                                                                                                                                                                                                                                                                                                                                                                                                                                                                                                                                                                                                     |
| Efficacy Evaluation              | 
L. loa microfilaremia determined via calibrated blood smears (CBS) pre-treatment and 2, 4, 6, 8, 10, 14 and 18 months after the first treatment. Blood samples for CBS will be obtained at around the same time between 11:00 and 15:00 o'clock to account for the diurnal variation of L.loa counts in the blood.
                                                                                                                                                                                                                                                                                                                                                                                                                                                                                                                                                                                                                                                                                                                                                                                                                                                          |

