## 5.3 Secondary endpoints

- Proportion of subjects whose microfilaria counts have been sustainably reduced to  $< 8100$  mf/ml by treatment group
- % of reduction in microfilaremia (range, median, Williams geometric mean) at each time point by treatment group by microfilaria level pretreatment and gender
- Microfilaria loads at each time point in each treatment group, compared by non-parametric tests because of the non-normal distribution of the *Loa* microfilaremia.
- Evolution of microfilaria counts in time

- Type, frequency and severity of adverse events (all adverse events and separate only those with a reasonable probability of relationship with study drug, see section 8.5).

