## 6.2 SUBJECT TREATMENT

### 6.2.1 Study drugs and treatment regimen

Albendazole 200 mg tablets and matching placebo will be provided by GSK. 4 tablets of active or placebo will be administered to each subject.

At 0, 2, 4, 6, 8 and 10 months, each subject will be administered after a standard fatty meal (one wheat fritter of 45-50 g filled with approximately 25 g of butter, commonly eaten by the local population and provided to participants as part of this study) orally either 800 mg of Albendazole or placebo, depending on the treatment group they have been randomized to.

| Time     | Group 1 | Group 2            | Group 3            |
|----------|---------|--------------------|--------------------|
| Month 0  | Placebo | Albendazole 800 mg | Albendazole 800 mg |
| Month 2  | Placebo | Albendazole 800 mg | Albendazole 800 mg |
| Month 4  | Placebo | Placebo            | Albendazole 800 mg |
| Month 6  | Placebo | Placebo            | Albendazole 800 mg |
| Month 8  | Placebo | Placebo            | Albendazole 800 mg |
| Month 10 | Placebo | Placebo            | Albendazole 800 mg |

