## **Protocol Amendment**

### **Efficacy of albendazole in decreasing *Loa loa* microfilaraemia**

The protocol of the study on the Efficacy of albendazole in decreasing *Loa loa* microfilaraemia started in March 2007 in the south Province of Cameroon. This study which was a double blind study had to continue until 18 month (September 2008). The study continued to this term and the blind was lifted. Due to tendency of decrease in one of the group, it was proposed that the follow-up should continue to 24 months with two supplementary control of the *Loa loa* microfilaremia at M21 and M24.

The procedure of blood sampling will remain as from M0 to M24. The blood sample will be collected almost and the same time, with the same material and with the same precautions. The examination of slides will follow the same procedures as the previous examinations.

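### Visit-by-visit tests of microfilaria load should be labelled exploratory, and at M2 and M4 the two albendazole groups, identically treated until then, should be pooled against placebo

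*Protocol*

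**What the plan says.** Three places in the protocol prescribe the same analysis. Section 9.2.1 states that "parasitaemia will be compared at each point between groups using non-parametric test". Section 5.3 lists it among the secondary endpoints: "Microfilaria loads at each time point in each treatment group, compared by non-parametric tests". The synopsis (section 1, Statistical Analysis) plans a comparison "between treatment groups at each time point with non-parametric tests due to non-normal distribution of mf loads".

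The synopsis sets smears at baseline and "2, 4, 6, 8, 10, 14 and 18 months after the first treatment", which is seven post-baseline visits. The amendment extends follow-up to 24 months "with two supplementary control of the" microfilaraemia, at M21 and M24. It records that the blind had been lifted and that a downward tendency in one group prompted the extension.

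For the responder endpoint, 9.2.1 limits testing to each active arm against placebo, and 9.1 sets alpha at 0.025 for each of those two comparisons. For the visit-wise loads the text speaks only of groups. It fixes neither the contrasts nor an error rate.

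Two further facts matter. Section 5.1 takes each smear in the dosing period before that visit's dose. The table in 6.2.1 gives Groups 2 and 3 the same treatment at Month 0 and again at the next dose: "Month 2 | Placebo | Albendazole 800 mg | Albendazole 800 mg". They diverge only with the Month 4 dose.

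**The concern.** A test repeated at seven visits for two regimens gives many chances for one small p-value. The protocol deals with multiplicity for the two primary tests. It then prescribes 7 to 21 further tests, depending on how the word groups is read, without saying how an isolated significant visit should be interpreted. The trial has 16 to 20 subjects per arm and a binary primary endpoint, so visit-wise p-values on the full counts will attract attention whatever the primary result. What is at stake is the reading of the secondary results.

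The second part follows from the protocol's own schedule. At M2 and M4 there are in effect two treatment conditions, placebo and albendazole so far, but the analysis as written keeps three groups. A test of Group 2 against Group 3 there can only produce a chance finding. A test of each regimen against placebo there uses only half of the subjects who have had the same exposure.

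**Working it through.** **The plan's own figures.** The protocol gives no error rate for the visit-wise tests. Its only related figure is the sample size in 9.1: 16 evaluable per arm, two-sided 0.025, placebo response below 1 in 10^6, active response 50%, power at least 90%. Exact power at 16 per arm is 96.2% for the uncorrected chi-square test and 89.5% for Fisher's test. Dropout gives 16 / (1 − 0.20) = 20. This is reproduced closely enough to use 16 to 20 per arm below. The two primary comparisons, if independent, have a joint error of 1 − 0.975² = 4.9%.

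**Number of visit-wise tests (main protocol).**
- One three-group test per visit: 7.
- Each regimen against placebo: 7 × 2 = 14.
- All three pairs: 7 × 3 = 21.
- Each regimen against placebo over nine visits: 9 × 2 = 18.

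**Simple bound for independent tests.** The chance of at least one false positive in m tests is 1 − (1 − α)^m.
- m = 14, α = 0.05: 1 − 0.95^14 = 51.2%.
- m = 14, α = 0.025: 1 − 0.975^14 = 29.8%.

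These overstate the rate, because the same subjects are measured repeatedly and both contrasts share the placebo arm.

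**Allowing for correlation.** The protocol gives no between-visit correlation, so 0.3 to 0.9 is an assumption. Simulation used three arms with no treatment effect, seven equally correlated visits and rank-sum tests (a Kruskal-Wallis test for the three-group version). The chance of at least one false positive is:

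| Case | 0.3 | 0.5 | 0.7 | 0.9 |
|---|---|---|---|---|
| 14 tests at 0.05, 20 per arm | 45.0% | 38.9% | 31.7% | 20.5% |
| 14 tests at 0.05, 16 per arm | 42.6% | 37.4% | 30.3% | 20.5% |
| 14 tests at 0.025, 20 per arm | 26.1% | 21.7% | 18.8% | 11.4% |
| 7 three-group tests at 0.05, 16 per arm | 26.6% | 23.3% | 18.7% | 12.3% |

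With nine visits, the 18 tests at 0.05 give about 22% to 52% over the same correlations, and about 44% at 0.5.

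**Exposure at M2 and M4.**

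| Smear | Doses already given, Group 2 | Doses already given, Group 3 |
|---|---|---|
| M2 | 1 albendazole | 1 albendazole |
| M4 | 2 albendazole | 2 albendazole |
| M6 | 2 albendazole, 1 placebo | 3 albendazole |

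The intestinal-helminth rule in 6.1.6.2 does not break this identity. The substitute dose it describes is the same 800 mg that both groups are assigned at Month 2.

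If Groups 2 and 3 are tested against each other at these two visits at 0.05, the chance of p ≤ 0.05 at one or both is about 7% to 9%. Two independent tests would give 1 − 0.95² = 9.75%.

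**Gain from pooling.** With 20 per arm and unit standard deviation, the variance of a difference in means is 1/20 + 1/20 = 0.100 for one active arm against placebo. Pooled, it is 1/40 + 1/20 = 0.075. The standard error falls by the factor √0.75 = 0.87. For an assumed shift of 0.7 standard deviations, rank-sum power at 0.05 rises from about 57% to about 69% (55% to 68% with a continuity-corrected statistic).

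**The case against.** The strongest reply is that multiplicity rules for secondary endpoints are commonly left to the statistical analysis plan, which is not at hand. That stands. A reader might infer that the missing hierarchy is itself an error, but the documents do not support this: the tests are listed as secondary, nothing calls them confirmatory, and no other section is contradicted.

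A reader might also infer that a chance significant visit is likely. For each regimen against placebo over the planned seven visits, the rate stays below one half in every correlated case examined. It passes one half only by adding the contrast between the two regimens or the two later visits at low correlation, or by treating the tests as independent.

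Nor is the primary result compromised. It is one responder endpoint with split alpha, and section 4 ties next steps to a sustained reduction of at least 50% and to safety, in a non-regulatory proof-of-concept study. A general linear model of the time course is also planned.

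It is tempting to name M18 as a formal key secondary visit. That does not follow. M18 is 18 − 2 = 16 months after Group 2's last active dose and 18 − 10 = 8 months after Group 3's, so the choice is debatable. With the blind already lifted, it would also be post hoc.

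Finally, the protocol never explicitly orders a test of Group 2 against Group 3. That is true, but a three-group test includes that contrast, and separate placebo comparisons forgo the pooled precision. The M2 and M4 point therefore holds under each reading.

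**Conclusion.** The point holds as a limited one about secondary analyses. Read at an unadjusted 0.05, the 14 comparisons with placebo carry about a 20% to 45% chance of at least one false significant visit, four to nine times the nominal 5%. At 0.025 the range is about 11% to 26%. These figures assume equal between-visit correlation of 0.3 to 0.9 and an unadjusted alpha, neither of which the protocol states. The primary endpoint and the go-forward rule are untouched.

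That Groups 2 and 3 have the same scheduled treatment before the M2 and M4 smears needs no such assumption. It follows from 5.1 and 6.2.1. Keeping them apart at those visits gains nothing and costs about 13% in standard error against placebo (1 − 0.87).

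**What to change.** Amend 9.2.1, with matching wording in 5.3 and the synopsis:

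- At M2 and M4, compare Groups 2 and 3 pooled with placebo, and make no test between Groups 2 and 3.
- State that all visit-wise comparisons of load, including M21 and M24, are exploratory. Report them as estimates with confidence intervals, and claim no single visit as evidence of efficacy by itself.
- Name no visit as a gated key secondary.

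With each regimen otherwise compared with placebo, this leaves 2 + 5 × 2 = 12 comparisons in the main protocol, or 16 with the two added visits. Both changes remain legitimate after unblinding: pooling rests on the dosing schedule and not on results, and the exploratory label only weakens claims. The cost is wording. The real downside is that a significant result at one visit can no longer stand alone as an albendazole effect. Separate regimen estimates at M2 and M4 are given up, but by then the regimens have not diverged.
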